#### Basis for sample size

We based our estimates for the main outcomes on data from our previous PTQ study among homeless smokers, as well as from the available literature [38, 43]. In the PTQ study, 7-day abstinence rates at week 26 were 9.3 % for the MI+NRT condition and 5.1 % for the control group. In another study [43] of alcohol-dependent smokers, our research team reported 7-day abstinence rates at 6 months as 9.1 % and 2.2 % for an intensive smoking intervention (three counseling sessions + NRT) and brief advice, respectively. We therefore projected the smoking abstinence rates as 4 % for the UC condition and 12 % for the IS condition. Our PTQ study also showed that the smoking abstinence rate for those who quit drinking during the study was nearly double that for drinkers, despite not having an alcohol intervention. We conservatively projected the smoking abstinence rate for the IntS+A condition as 18 %. We based the projection for the alcohol abstinence rates on a study [38] in which our research team found 90-day alcohol abstinence rates of 32–43 % at 12 months among alcohol-dependent smokers.

### Data analysis

Before initiating outcome analyses of quantitative data, we will examine distributions for all variables, with particular attention to variable ranges, missing values, skewness and transforming variables when indicated according to the criteria of Winer [44]. Using analysis of variance (ANOVA) for continuous data and χ^2^ tests for categorical data, we will examine group comparability at baseline to determine whether randomization was successful in creating equivalent groups with regard to demographic, process and important independent variables such as education, income and literacy levels. These data will help determine if there is a need to incorporate stratifying variables or covariates into later analyses.

#### Analyses for primary hypotheses

The primary analysis will be based on an intention-to-treat analysis; that is, participants will be analyzed regarding the treatment to which they were randomized. The intervention effects for the primary outcomes of week 52 biochemically verified 7-day abstinence from cigarette smoking and week 52 ninety-day abstinence from alcohol consumption will be tested using χ^2^ tests. Any participants lost to follow-up will be classified as treatment failures (i.e., smoker or drinker). Bonferroni procedures will be used to control for experiment-wise type I error rate. Abstinence rates and corresponding 95 % confidence intervals will be estimated and summarized using appropriate tabular and graphical methods.

In supportive analyses, we will examine baseline variables, including demographics (age, sex, income and education), nicotine dependence, withdrawal symptoms, motivation and confidence, self-efficacy, social support, perceived stress and depressive symptoms, in terms of their relationship to study outcomes. Analyses accounting for these measures will be conducted using multiple logistic regression including intervention groups as controlled factors. Thus, we will be able to assess whether the main conclusions from the primary analysis are robust for the inclusion of these baseline variables. Fisher’s exact test will be used to compare the biochemically verified 7-day smoking abstinence rates at week 52 follow-up between the IS and UC participants. Supportive analysis will be conducted using multiple logistic regression including the intervention group as a predictor, adjusting baseline covariates to assess whether the result from secondary analysis is robust for the inclusion of baseline covariates.

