In our recently completed Power to Quit (PTQ) study (*N* = 430) [32, 33] targeting homeless smokers, we found cotinine-verified 7-day quit rates to be 9.3 % for motivational interviewing (MI) vs. 5.6 % for the control group at 26 weeks. These quit rates are low when compared with those in the general population, demonstrating the challenge for a smoking intervention in homeless populations. A variety of factors may have contributed to low quit rates in the study, including (1) high level of nicotine dependence as indicated by mean 20 cigarettes per day and 87 % of the participants smoking their first cigarette within 30 minutes of awakening, (2) high rates of substance abuse and psychiatric comorbidities [18, 19], (3) competing daily social needs and (4) need for more cognitive behavioral strategies instead of MI, given the high baseline motivation to quit (9+ on a 1–10 scale). The low quit rates revealed in studies of alcohol-dependent and homeless smokers, along with positive outcomes in studies of combined NRT, suggest that a more intensive intervention ought to be considered. The primary aim of the present study is therefore to evaluate the effects of an intensive smoking intervention that integrates alcohol abuse treatment and smoking cessation in a homeless population. We will use a three-group randomized design to test the study hypotheses in a community-based setting. The three study conditions are (1) integrated intensive smoking intervention using cognitive behavioral therapy (CBT) plus alcohol intervention (IntS+A), (2) an intensive smoking (IS) intervention using CBT or (3) usual care (UC; brief smoking cessation and brief alcohol counseling, both based on U.S. Public Health Service [USPHS] guidelines) [34, 35]. In addition, all participants will receive a 12-week treatment with a combination of nicotine patch plus gum or lozenge.

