### Statistical analyses and sample size and power calculations

For this study, 645 participants will be randomized at baseline to test the main effects of smoking and alcohol interventions for the primary smoking outcome (cotinine-verified 7-day smoking abstinence at week 52 follow-up) and alcohol outcome (breathalyzer-verified continuous alcohol abstinence for 90 days at week 52 follow-up). The study is powered to test the primary hypotheses using χ^2^ tests and the secondary hypothesis using Fisher’s exact test. Assuming a two-sided χ^2^ test with a type I error rate of 0.025 for each of two primary outcomes, smoking abstinence rates of 18 % in the IntS+A group versus 8 % in the IS group and 4 % in the UC group, a sample size of 215 participants in the IntS+A group and 430 participants in the IS and UC combined group will achieve a power of 80 %. With 645 participants and a type I error rate of 0.025, we have greater than 90 % power for the primary alcohol hypothesis, assuming 90-day alcohol abstinence rates of 32 % vs. 10 % for the IntS+A group versus the IS intervention or UC groups . Assuming a two-sided Fisher’s exact test with a type I error rate of 0.05 for the secondary outcome of smoking abstinence rate of 12 % in the IntS group versus 4 % in the UC group, a sample size of 215 participants per group will achieve a power of 82 %. Our sample size calculation was based on the analysis that classified those lost to follow-up as smokers or drinkers and therefore has accounted for up to a 25 % attrition rate observed in the prior Power to Quit (PTQ) study [32, 33].

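### Optional improvement: the primary smoking comparison could adjust for baseline nicotine dependence, for a small gain in power at almost no cost

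*Protocol article*

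**What the plan says.** All references are to the protocol article.

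- *Analyses for primary hypotheses* names as primary "The intervention effects for the primary outcomes of week 52 biochemically verified 7-day abstinence from cigarette smoking", together with "week 52 ninety-day abstinence from alcohol consumption will be tested using χ^2^ tests". No covariate enters either test.
- The same section then lists baseline variables for supportive multiple logistic regression. Besides demographics, these are "nicotine dependence, withdrawal symptoms, motivation and confidence, self-efficacy, social support, perceived stress and depressive symptoms". The stated purpose is to see whether the main conclusions are robust.
- *Background* lists four possible contributors to the low quit rates in the previous study. The first is "high level of nicotine dependence as indicated by mean 20 cigarettes per day". It also reports that 87 % of those participants smoked within 30 minutes of waking.
- *Randomization process* describes blocked allocation and mentions no stratification.
- *Statistical analyses and sample size and power calculations* bases power on the chi-square test, "with a type I error rate of 0.025 for each of two primary outcomes".

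**The concern.** Nicotine dependence is a plausible predictor of abstinence and is collected at baseline, yet nothing stated in the design balances it between arms and the primary test does not use it. Any chance imbalance therefore enters the primary estimate.

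A prespecified adjustment for a prognostic baseline variable removes that part of the noise and leaves the type I error where it was. In a supportive analysis the adjustment can comment on the primary conclusion but cannot sharpen it. At stake is a modest amount of power, not the validity of the trial.

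**Working it through.** **Inputs**

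- Contrast: "a sample size of 215 participants in the IntS+A group and 430 participants in the IS and UC combined group".
- Two-sided alpha 0.025, so the critical value is z = 2.241.
- Rates in the power statement: 18 % "in the IntS+A group versus 8 % in the IS group and 4 % in the UC group". The pooled control rate is (8 + 4)/2 = 6 %.
- Rates in *Basis for sample size*: the article "projected the smoking abstinence rates as 4 % for the UC condition and 12 % for the IS condition". The pooled control rate is (12 + 4)/2 = 8 %.
- Prognostic strength of dependence for week-52 abstinence: not in the article. **Assumption:** odds ratio per SD of 0.7, 0.5 or 0.4 on a normally distributed score.

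**Step 1. Power of the planned chi-square.** Power = Φ[(p1 − p2 − z·SE0)/SE1], with SE0 from the pooled rate and SE1 from the separate rates.

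- 18 % vs 6 %: pooled rate 0.100, SE0 = √(0.100 × 0.900 × (1/215 + 1/430)) = 0.0251, SE1 = √(0.18 × 0.82/215 + 0.06 × 0.94/430) = 0.0286. Then (0.12 − 2.241 × 0.0251)/0.0286 = 2.23, power 98.7 %.
- 18 % vs 8 %: pooled rate 0.113, SE0 = 0.0265, SE1 = 0.0293. Then (0.10 − 2.241 × 0.0265)/0.0293 = 1.39, power 91.7 %.

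Neither equals the stated 80 %. A pairwise 18 % vs 8 % with 215 per arm gives 80.3 %. That mismatch, and the two different IS rates, are a separate matter. Here they mean only that both rate sets must be shown.

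**Step 2. How much a covariate can explain.** The effective sample size grows by about 1/(1 − R²), where R² is the share of outcome variance explained. Direction does not matter, so an odds ratio of 0.5 equals 2.0 and 0.4 equals 2.5.

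| Odds ratio per SD | R², 18/8/4 % | Gain | R², 18/12/4 % | Gain |
|---|---|---|---|---|
| 1.5 | 0.0151 | 1.5 % | 0.0167 | 1.7 % |
| 2.0 | 0.0448 | 4.7 % | 0.0490 | 5.2 % |
| 2.5 | 0.0779 | 8.4 % | 0.0843 | 9.2 % |

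**Step 3. Simulated power.** Three arms of 215, 4,000 trials per setting, Pearson chi-square vs the covariate-adjusted logistic score test. Entries are power in %, unadjusted → adjusted.

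| IntS+A/IS/UC | OR 0.7 | OR 0.5 | OR 0.4 |
|---|---|---|---|
| 18/8/4 % (article) | 99.2 → 99.3 | 99.1 → 99.2 | 99.0 → 99.4 |
| 18/12/4 % (article) | 92.4 → 92.7 | 92.3 → 93.4 | 92.6 → 94.1 |
| 13.5/9/3 % (assumed) | 81.3 → 82.0 | 81.5 → 83.7 | 81.9 → 85.1 |
| 14/12/4 % (assumed) | 54.3 → 55.0 | 55.4 → 57.7 | 54.7 → 58.4 |

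A further assumed case, 15 % vs 8 %, gave 68.8 → 69.6, 68.1 → 70.1 and 67.8 → 71.5 at odds ratios of 1.5, 2.0 and 2.5. Simulation error is about 0.1 to 0.6 points, so the smallest differences are not distinguishable from zero.

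**Step 4. Type I error.** With 8 % in all arms (8,000 runs, nominal 2.5 %), the chi-square rejected in 2.39 % and the adjusted score test in 2.31 %.

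**Step 5. The choice of test matters.** An adjusted likelihood-ratio test set against a Pearson chi-square can look like a loss. At 18/12/4 % with a covariate of no prognostic value, power was 92.4 % vs 91.8 %. The unadjusted likelihood-ratio test is itself 0.6 to 1.8 points below Pearson at 18/12/4 % and at 15 % vs 8 %. The apparent loss comes from changing the test, not from adjusting.

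**Step 6. A coarse marker gains little.** Suppose dependence is coded as 87 % vs 13 %, with assumed quit rates of 9.1 % and 17 % (odds ratio about 2). The overall rate is 0.87 × 0.091 + 0.13 × 0.17 = 0.101. Then R² = 0.87 × 0.13 × (0.17 − 0.091)²/(0.101 × 0.899) = 0.8 %. Simulated gains with odds ratios of 2 and 3 were 0.2 and 0.8 points at 18/12/4 %, and 0.04 and 0.2 points at 18/8/4 %.

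**The case against.** The case for leaving the plan alone is strong, and most of it stands.

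- The planned test is valid and agrees with its power basis. Chance imbalance affects every unadjusted randomized comparison, and the type I error already allows for it. **Stands.**
- A logistic regression including dependence is already planned. **Stands in part.** It is supportive only, and its list runs to about 12 measures. The article's rates imply 215 × 0.30 ≈ 65 or 215 × 0.34 ≈ 73 quitters. If all 12 entered together with two arm terms, that would be about 5 events per parameter. The article does not say they would. A single named covariate avoids the question.
- The gain depends on an assumed prognostic strength. The Background's wording is hedged, and uniformly high dependence could explain a low overall rate without separating quitters from non-quitters. Counting dropouts as smokers may weaken the association further. **Stands.**
- Gains above 2 points come from rates the article does not give. The 13.5/9/3 % set is 0.75 times 18/12/4 %, although the article says attrition is already allowed for. **Stands**, so those rows only illustrate a smaller true effect.

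A reader might infer that the chi-square is wrong or biased, that the trial forgoes substantial precision, or that the sponsor names dependence as an established cause. The article supports none of these: the test holds its level, the gain at the article's own rates is under 2 points, and the Background says only that four factors may have contributed.

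**Conclusion.** This is an optional improvement, not an error. Within the assumed odds ratios of 0.7 to 0.4 per SD, adjustment adds under 0.5 points of power at 18/8/4 % and about 0 to 1.6 points at 18/12/4 %. It adds about 1 to 4 points only if the true effect is smaller than projected, where unadjusted power is roughly 55 to 82 %. Type I error stays near the nominal 2.5 %.

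The result assumes a graded, roughly normal dependence score and a score test. With a binary marker split 87/13, the gain was below 1 point in every case run. The standardized risk difference suggested for reporting was not itself simulated.

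**What to change.** In *Analyses for primary hypotheses*, before outcome data are seen:

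1. Make the primary smoking comparison (IntS+A vs IS and UC combined) the score test from a logistic regression with one prespecified baseline covariate, a named graded measure of nicotine dependence, not a binary 30-minute marker.
2. Report the standardized (marginal) risk difference with its confidence interval.
3. Keep the unadjusted chi-square as a supportive analysis.

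The cost is plan wording and a little programming, with no new data and no change in sample size. The small downside is that the covariate must be operationally defined (the article names no scale) and complete at baseline, with a stated rule such as single imputation for the few gaps. *Trial status* places recruitment in its first phase, so the change was feasible when the article was written.

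### The fixed 0.025 split between the two primary outcomes is valid but needlessly conservative; Holm keeps the same 0.05 bound and can only add power for smoking

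*Protocol article*

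**What the plan says.** All references are to the protocol article.

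- Multiplicity, under Analyses for primary hypotheses: "Bonferroni procedures will be used to control for experiment-wise type I error rate". Both primary outcomes are tested by χ² tests, and participants lost to follow-up count as failures.
- Alpha, under Statistical analyses and sample size and power calculations: "Assuming a two-sided χ^2^ test with a type I error rate of 0.025 for each of two primary outcomes".
- Smoking rates in that section: "smoking abstinence rates of 18 % in the IntS+A group versus 8 % in the IS group and 4 % in the UC group", with "a sample size of 215 participants in the IntS+A group and 430 participants in the IS and UC combined group" and a stated power of 80 %.
- Alcohol in that section: "we have greater than 90 % power for the primary alcohol hypothesis", on 32 % vs 10 %.
- Basis for sample size gives a different rate for the IS group: "We therefore projected the smoking abstinence rates as 4 % for the UC condition and 12 % for the IS condition". IntS+A stays at 18 %.

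Taken together, the alpha statement and the Bonferroni statement describe a fixed equal split: smoking is tested at 0.025 whatever the alcohol result.

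**The concern.** Under a fixed split, alpha assigned to one outcome is not reused once that outcome has been shown. That matters most when the two tests have very unequal power, as they do here on the plan's own rates: the alcohol test is close to certain to succeed, while smoking is the outcome with only 80 % stated power. Holm's procedure tests the smaller p-value at 0.025 and, if that is significant, the other at 0.05. The experiment-wise error that the plan sets out to control has the same 0.05 bound, so the unused alpha could go to smoking without breaching it. At stake is power on one primary outcome, not the validity of the analysis.

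**Working it through.** **Method.** Power of the χ² test of IntS+A (215) against IS and UC combined (430), by exact enumeration with each control arm at its own rate. As a check, the normal approximation: power = Φ[(|p1 − p2| − z·s0)/s1], where s0 is the standard error at the pooled rate, s1 the standard error at the separate rates, z = 2.2414 for two-sided 0.025 and z = 1.9600 for 0.05.

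**Step 1. The plan's own figures.**
- Alpha: 0.025 + 0.025 = 0.05. Correct.
- Alcohol, 32 % vs 10 %, alpha 0.025: s0 = 0.03162, s1 = 0.03495; (0.22 − 2.2414 × 0.03162)/0.03495 = 4.27, so power is about 99.999 % (exact 99.9996 %). The stated figure of more than 90 % is correct and understated.
- Smoking, power-section rates: the combined control rate is (8 + 4)/2 = 6 %. s0 = 0.02506, s1 = 0.02860; (0.12 − 2.2414 × 0.02506)/0.02860 = 2.23, so power is 98.7 % (exact 99.1 %). The stated 80 % is not reproduced.
- Smoking, Basis rates: the combined control rate is (12 + 4)/2 = 8 %. s0 = 0.02648, s1 = 0.02929; (0.10 − 2.2414 × 0.02648)/0.02929 = 1.39, so power is 91.7 % (exact 92.6 %). Again not 80 %.

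**Step 2. Error control.**
- With no effect on either outcome, Holm makes at least one false rejection exactly when Bonferroni does. For independent outcomes this is 1 − 0.975² = 0.0494; simulation gives about 0.036 at a correlation of 0.9.
- With a true alcohol effect and no smoking effect, smoking is falsely rejected at up to 0.05, within the bound.
- Any p-value at or below 0.025 is rejected under both procedures, so Holm loses no rejection.

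**Step 3. Smoking power under Holm.** Treating the two tests as independent, power = P(0.025) + [P(0.05) − P(0.025)] × A, where A is alcohol power at 0.025. On the plan's alcohol rates A is practically 1, so Holm power equals P(0.05).

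| Smoking inputs (IntS+A / IS / UC) | Fixed 0.025 | Holm | Gain, points |
|---|---|---|---|
| 18 / 8 / 4 %, power section | 99.1 % | 99.6 % | about 0.5 |
| 18 / 12 / 4 %, Basis for sample size | 92.6 % | 95.6 % | about 3 |
| Stated 80 % at face value | 80.0 % | 86.9 % | about 7 |
| Assumption: 14.4 / 8 / 4 % | 88.6 % | 93.1 % | about 4.5 |
| Assumption: 14.4 / 12 / 4 % | 60.9 % | 70.6 % | about 10 |

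Face-value row: 80 % power at 0.025 means a standardised effect of 2.2414 + 0.8416 = 3.0830; at 0.05 the power is Φ(3.0830 − 1.9600) = Φ(1.1230) = 86.9 %. The 14.4 % is not in the documents. It is 0.8 × 18 %, used only to show what happens if the smoking effect falls short.

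**Step 4. Dependence on the alcohol effect.** Control is held at 10 % and the stated 80 % smoking power is the baseline.

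| IntS+A alcohol abstinence | Alcohol power at 0.025 | Smoking power under Holm |
|---|---|---|
| 32 % | >99.9 % | 86.9 % |
| 25 % | >99 % | 86.9 % |
| 20 % | about 88 % | 86.1 % |
| 16 % | 49 % | 83.4 % |
| 12 % | 8 % | 80.5 % |
| 10 % (no effect) | 2.5 % | 80.2 % |

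The gain fades as the alcohol effect fades and never becomes a loss.

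**The case against.** The strongest reply is that nothing here is wrong. The two sections agree with each other, Bonferroni controls the error rate it is meant to control, and a conservative pre-specified rule is a legitimate choice. That stands: a reader might infer from this point that the primary analysis is invalid, and the documents do not support that.

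Four further objections have force.

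- **Size.** On the power section's own rates the gain is half a point. A reader might quote only the gain of 7 or 10 points. The 7 depends on a stated 80 % that does not follow from the section's rates and group sizes; the 10 depends on an assumed rate. One might explain the 80 % as 18 % vs 8 % with 215 in each group, which gives 80.3 % (87.2 % at 0.05). But the text attaches the 80 % to 215 vs 430, and other undescribed routes also land near it, such as both rates cut by a quarter (13.5 % vs 6 %: 81.0 %). That explanation is a guess.
- **The alcohol assumption.** The 32 % comes from alcohol-dependent smokers, whereas the text on additional eligibility criteria excludes current alcohol dependence, and no source is given for the 10 %. That smoking would almost always be tested at 0.05 therefore holds on the stated rates only.
- **Cost.** A reader might infer that Holm has no downside. Smoking's own false-positive rate can rise from 0.025 to 0.05 when alcohol treatment truly works, the smoking claim no longer stands wholly apart from the alcohol result, and matching simultaneous intervals are less simple. The bound on experiment-wise error is unaffected, as are the 95 % intervals for abstinence rates that the plan promises.
- **Wording.** The phrase on Bonferroni procedures could be stretched to cover Bonferroni–Holm, and an analysis plan not shown here might say so. The explicit 0.025 for each outcome points to the fixed split; if Holm was meant, a sentence would settle it.

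None of these gives a setting in which Holm has less power than the fixed split.

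**Conclusion.** A cheap improvement, not an error in the plan. The fixed split is valid and more conservative than the 0.05 experiment-wise bound requires. Holm would add about 0.5 points of smoking power on the power section's rates, about 3 on the Basis rates, and about 7 if the stated 80 % is right. The gain is larger if the smoking effect falls short while the alcohol effect holds. These figures assume 32 % vs 10 % for alcohol; with a smaller alcohol effect they shrink toward zero. The spread itself reflects the unresolved conflict over the IS rate (8 % or 12 %) and the 80 % that neither set of rates reproduces. That is a separate matter, and changing the multiplicity procedure does not resolve it.

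**What to change.** Under Analyses for primary hypotheses, replace the Bonferroni sentence with one to this effect: the two primary outcomes will be tested by Holm's procedure at an experiment-wise two-sided level of 0.05, with the smaller p-value compared with 0.025 and, only if it is significant, the other compared with 0.05.

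Keep 0.025 as the planning alpha in the sample size section; it is then conservative and no recalculation is needed on this account. Record the change before any outcome data are examined. The article places the trial in its first phase of recruitment and the primary outcomes are measured at week 52, so this looks feasible.

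The cost is one sentence, with no change to sample size, visits or outcomes. The sponsor should accept knowingly that smoking's individual error rate can reach 0.05 and that simultaneous intervals matching the test are less simple than under the fixed split.

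### Secondary IS vs UC comparison: Fisher's exact test is valid, but an uncorrected chi-square or Boschloo test would give 2 to 7 points more power at no cost

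*Protocol article*

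**What the plan says.** Two sections of the protocol article fix the test, and they agree.

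- Under 'Statistical analyses and sample size and power calculations': "The study is powered to test the primary hypotheses using χ^2^ tests and the secondary hypothesis using" Fisher's exact test. The secondary calculation is for a two-sided Fisher's "exact test with a type I error rate of 0.05 for the secondary outcome", with a "smoking abstinence rate of 12 % in the IntS group versus 4 % in the UC group". It concludes that "a sample size of 215 participants per group will achieve a power of 82" per cent.
- Under 'Analyses for primary hypotheses', Fisher's exact test "will be used to compare the biochemically verified 7-day smoking abstinence rates at week 52 follow-up between the IS and UC participants". A covariate-adjusted logistic regression supports this comparison. The same section uses chi-square tests for the primary outcomes and counts anyone lost to follow-up as a smoker or drinker.

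The arm called IntS in the power statement is read here as the IS arm, because 'Basis for sample size' says "We therefore projected the smoking abstinence rates as 4 % for the UC condition and 12 % for the IS condition". Neither section gives a reason for using a different test here than for the primary comparison of the same endpoint.

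**The concern.** Fisher's test conditions on the total number of abstainers. The reference distribution is then coarse, and with low event rates the true error rate falls well below the nominal 5 %. The unused part of that 5 % is lost power.

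The comparison matters because it is the only powered one that isolates intensive smoking CBT from usual care. The primary smoking calculation sets IntS+A against IS and UC combined. The choice of test can also decide the result in tables close to the projected rates, as the example in the working shows.

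**Working it through.** **Inputs.** 215 per arm; two-sided alpha 0.05; 12 % (IS) vs 4 % (UC), all from the sample size section. Because lost participants count as smokers, the denominator stays at 215. The 8 % vs 4 % scenario uses the IS and UC rates in the article's own primary smoking calculation.

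**1. The stated power.** The usual two-proportion formula, with mean rate 0.08 and difference 0.08, at 82 % power:

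n₀ = [1.960·√(2·0.08·0.92) + 0.915·√(0.12·0.88 + 0.04·0.96)]² / 0.08² = 188.8

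With the continuity correction that approximates Fisher's test:

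n = (n₀/4)·[1 + √(1 + 4/(n₀·0.08))]² = 213.1, so 214 per arm

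The article has 215. Its 82 % therefore reproduces and belongs to Fisher's test.

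**2. Expected counts.** 215 × 0.12 = 25.8 and 215 × 0.04 = 8.6 abstainers; pooled, (25.8 + 8.6)/2 = 17.2 per arm. These are not sparse cells.

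**3. Exact size.** All 216 × 216 possible outcomes were enumerated. The rejection probability is the sum of Bin(215, p₁) × Bin(215, p₂) over the tables that the test rejects. With p₁ = p₂:

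| Common rate | Fisher | Uncorrected Pearson chi-square |
|---|---|---|
| 4 % | 2.7 % | 4.96 % |
| 6 % | 3.1 % | 4.76 % |
| 8 % | 3.3 % | 4.85 % |
| 12 % | 3.6 % | 5.00 % |
| Maximum over all rates | 4.1 % | 5.17 % (near 39 %) |

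Between 2 % and 15 % the chi-square size is at most 5.01 %. Boschloo's test uses Fisher's p-value as its statistic and raises the cut-off as far as the 5 % limit allows. Here the cut-off is 0.0607 (0.06073 before rounding) and the maximum size is 4.95 %.

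**4. Exact power.**

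| Rates | Fisher | Boschloo | Uncorrected chi-square |
|---|---|---|---|
| 12 % vs 4 % | 84.5 % | 86.9 % | 88.0 % |
| 8 % vs 4 % | 34.4 % | 38.2 % | 41.1 % |

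Over Fisher, the gain is 2.4 points (Boschloo) or 3.5 points (chi-square) at the planned rates, and 3.8 or 6.7 points at 8 % vs 4 %. A Yates-corrected chi-square gains nothing at the planned rates (84.5 %).

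**5. A table where the choice decides.** Take 20 vs 9 abstainers of 215 each (9.3 % vs 4.2 %). The pooled rate is 29/430 = 0.0674, and chi-square = (11/215)² / (0.0674 × 0.9326 × 2/215) = 4.47, p = 0.034. Fisher gives p = 0.053. Boschloo also rejects, since 0.053 is below 0.0607.

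**The case against.** The case for leaving the text alone is strong on several points.

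- **Nothing is misstated.** A reader might infer from a true size near 3 % that the article reports a wrong error rate. It does not. An alpha of 0.05 is a ceiling, Fisher's test respects it, and the stated power was computed for Fisher and is slightly conservative. This stands in full.
- **No participants are wasted.** A reader might convert the lost power into participants recruited needlessly. The article does not support that: 215 per arm also serves the primary comparison of 215 with 430, so changing the secondary test would not shrink the trial.
- **The assumed rates matter far more than the test.** A reader might infer that the test decides whether this comparison is adequately powered. For the two pairs of rates in 'Basis for sample size', Fisher and chi-square give 32.6 % and 38.8 % at 9.3 % vs 5.1 %, and 86.0 % and 89.9 % at 9.1 % vs 2.2 %. Either both tests are inadequate or both are adequate.
- **A supportive logistic regression is planned.** It does not carry Fisher's discreteness penalty, but it supports the formal test and does not replace it.
- **Chi-square gives up the strict guarantee.** Its size can reach 5.17 %, though only near a 39 % rate. Boschloo answers this: it rejects whenever Fisher does and still holds 5 %.

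What remains is an avoidable loss of efficiency.

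**Conclusion.** This is a cheap, optional improvement and not a defect in the plan. Fisher's test for IS vs UC is valid, prespecified consistently in both sections, and powered above 80 % under the article's 12 % vs 4 % assumption. It nevertheless leaves part of the 5 % level unspent, and a test with 2.4 to 3.5 points more power at the planned rates is available without further data. The size of the gain rests on 215 analysed per arm, losses counted as smokers, a two-sided 0.05 level, and the rates shown. If the IS rate is nearer 8 %, the gain is up to 6.7 points, but power stays low with every test.

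**What to change.** Before unblinding, change the IS vs UC test in both sections ('Statistical analyses and sample size and power calculations' and 'Analyses for primary hypotheses') to one of these:

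- **Pearson chi-square without continuity correction**, matching the test for the primary outcomes, with power restated as about 88 % (exact calculation). The wording must say uncorrected, because the Yates version gives the gain back. The downside is a true size of up to 5.2 % near a 39 % rate, and at most about 5.0 % at the rates expected here.
- **Boschloo's exact test**, if a guaranteed 5 % level is wanted, with power restated as about 87 %. The downside is only computing time.

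In either case keep Fisher's test as a sensitivity analysis. The cost is one line of wording in each section; the sample size, visits and data collection do not change.
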